### Challenges in linking agriculture

The most recent evaluation of the GSFP undertaken in 2012 identified the need for ‘a more strategic approach in linking farmers to the programme’ [10]. This gap between the food production side and the caterers has been documented in other studies as well, including a recent supply chain analysis that highlighted a number of key constraints in the current model (Fig. 1), including:Mismatch of cash flow: farmers need money as soon as they harvest. Caterers receive money after serving childrenLack of trust between farmers and caterers (especially for future payments): farmers do not trust caterers to advance food for later payment. Inconsistent payment from government worsen their perceptionsDifficult for caterers to access farmers: no contact information, difficult to reach, widely spread out, a lot of interaction necessaryNo structure in place to facilitate caterer and farmer negotiations

**Fig. 1 Fig1:**
[figure not shown]
Missing link in the Ghana School Feeding Programme (GSFP) supply chain [8]

### The HGSF pilot

An innovative capacity-building component is being integrated alongside the GSFP and constitutes one of the treatment arms of the experiment. The details of the pilot were developed by a multi-disciplinary working group composed of in-country stakeholders under government leadership. This pilot involves the development of an integrated package of community-level activities aimed at enhancing the impact of the GSFP on poverty and food insecurity and involves two main components [11].Agriculture: this component is designed to stimulate the economy at community level by purchasing food from smallholder farmers. The component aims to bring the actors of the school feeding supply chain and GSFP community programme together to discuss the demand and supply needs to the school feeding market. Farmers and caterers would then be able to negotiate a price and payment agreement to address the issue of mistrust. This agreement will be backed by a master contractNutrition: this component will include activities to improve the nutritional quality of the school meals (e.g. menu planning), promotion of improved health, nutrition and hygiene behaviours (e.g. behaviour change campaigns), and the provision of multiple micronutrient fortification

## Methods

### Programme theory of the intervention

School feeding interventions linked to smallholder agriculture can have multiple goals in the following areas:Education: increasing school enrolment, attendance and reducing drop-out, and improving cognition and learning achievementHealth: improving nutritional status of school age childrenAgriculture: supporting incomes of recipient households (those consuming food) and farmer households (those providing the food)Small enterprise development: supporting incomes of caterers and cooks involved in the food service provision

Figure 2 illustrates in very broad terms the impact theory of school feeding on agriculture, education, and health. School feeding affects educational outcomes directly by increasing enrolment, attendance and completion (line ‘a’ in the figure). It affects health directly by improving nutritional status (line ‘b’); this in turn has an indirect impact on education, as improving nutritional status has a positive impact on learning outcomes (line ‘d’). The intervention can also affect income directly by increasing households’ food security (line ‘c’). In addition, the intervention can benefit the small enterprises involved in the school food service provision. Finally, there are effects running through increased income and health and nutrition and vice versa, as richer families are investing more in human capital and more educated and healthier adults are more economically productive (lines ‘e’). However, these latter effects (represented as dotted lines in Fig. 2) only occur in the long term and certainly not before children have left school: therefore, we will not discuss them in the following design. Whilst the evidence base on the effects on child education, health and nutrition is generally well-established (see [12] for a recent systematic review) this evaluation is the first to also examine the effects on agriculture and enterprise development.

**Fig. 2 Fig2:**
[figure not shown]
Overall programme theory of school feeding interventions

It must be emphasised that the ability of the school feeding intervention to deliver the effects depicted in Fig. 2 critically depends on the appropriate implementation of the programme. The management and implementation of the intervention involves several actors, and there is evidence that in Ghana there are several problems of information flow, supervision and monitoring between these different stakeholders. Programme success will also depend on the ability of communities to actively engage in the programme and in the strengthening of the public institutions involved.

### Main hypotheses and outcome indicators

We summarise here the expected impact of the intervention on education, nutrition and agriculture as captured in the programme theory. The detailed programme theory for the different domains is captured in [13].

### Education

The intervention will have a positive impact on enrolment, attendance and drop-out ratesThe intervention will have an impact on cognitive abilities and class behaviour including attentionThe impact on learning (test scores) will be moderate as school quality is unlikely to change in the short term

### Nutrition and health

The intervention will have a limited impact on physical growth of children because of the increase in physical activity levels (PAL), substitution effects and the age range (5–15 years) of the targeted population. An impact on siblings of school-going children is possible if substitution effects are strongThe intervention will have a moderate impact on the diet because on the one hand, food purchases by caterers do not follow nutritional guidelines, and on the other nutrition education will be a component of the school-level trainingsThe intervention will have some impact on micronutrient status where the food provision is fortified, and only moderate effects on diet diversity are expected

### Agriculture and community development

The intervention will have an impact on a small number of farmers in the intervention communities. Other persons in the community may benefit either directly or indirectly via an increase in incomeThe programme will have an impact on a small number of caterers involved in the school feeding service provision

In addition to examining the potential effects in the different domains, the evaluation will also assess the pathways through which these effects are mediated.

Table 1 includes a list of the main outcome indicators of the study. The data collection section below describes how data will be collected using different survey instruments. All the main study outcomes, including school enrolment, attendance and test scores, will be obtained through the household- and child-level interviews.

**Table 1 Tab1:** Primary indicators for the evaluation

Type	Domain	Indicator
Impact	Agriculture	Household income, production, sales
	Education	Child enrolment, attendance, completion, maths and literacy scores (5–15 year olds)
	Cognition	Raven’s test and forward/backward digit span scores (5–15 year olds)
	Physical health/Nutrition	Anthropometry (height-for-age, BMI-for-age, 2–15 year olds), haemoglobin levels (5–15 year olds)
Outcome	Food consumption	Nutrient adequacy and dietary diversity score (individual and household)
Output	Meal service	Quality of school meals, portion sizes, frequency and timeliness

For the pathways analysis, in addition to the outcome indicators in Table 1 we will also observe the programme impact on intermediate indicators, particularly for those outcomes that are more difficult to observe directly. In the case of farmer income, we will look at several intermediate outcomes such as input use (labour, land, seeds and fertiliser), investments (farm capital such as tools and machinery), and market access (marketed surplus, prices and markets). In terms of other intermediate indicators in the nutrition and health pathway, we will observe the effect of the programme on knowledge and practices of caterers and school management members, and on the quantity, quality, and timeliness of the preparation and delivery of the school meals.

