## Abstract

**Background:**

‘Home-grown’ school feeding programmes are complex interventions with the potential to link the increased demand for school feeding goods and services to community-based stakeholders, including smallholder farmers and women’s groups. There is limited rigorous evidence, however, that this is the case in practice. This evaluation will examine explicitly, and from a holistic perspective, the simultaneous impact of a national school meals programme on micronutrient status, alongside outcomes in nutrition, education and agriculture domains.

The 3-year study involves a cluster-randomised control trial designed around the scale-up of the national school feeding programme, including 116 primary schools in 58 districts in Ghana. The randomly assigned interventions are: 1) a school feeding programme group, including schools and communities where the standard government programme is implemented; 2) ‘home-grown’ school feeding, including schools and communities where the standard programme is implemented alongside an innovative pilot project aimed at enhancing nutrition and agriculture; and 3) a control group, including schools and households from communities where the intervention will be delayed by at least 3 years, preferably without informing schools and households. Primary outcomes include child health and nutritional status, school participation and learning, and smallholder farmer income. Intermediate outcomes along the agriculture and nutrition pathways will also be measured. The evaluation will follow a mixed-method approach, including child-, household-, school- and community-level surveys as well as focus group discussions with project stakeholders. The baseline survey was completed in August 2013 and the endline survey is planned for November 2015.

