### Markets

Early studies of food prices in Ghana found negligible price differences across the country [18]. Regional equality of consumer prices, however, does not imply the equality of producer prices at a more localised level. The ability of market interventions to influence local price dynamics depends on the level of spatial market integration between local markets. Abdulai [19] analysed the maize market in Ghana and found a high level of integration, meaning a quick transmission of prices from one locality to the other. In these circumstances large purchases of staple food in localised markets are unlikely to produce price changes. Cudjoe et al. tested for market integration for several staple foods in Ghana and found a high level of integration for rice and maize but much less for tubers such as cassava and yam [20]. Prices of the latter items may be strongly localised and transmission between markets may not be easy. It should also be noted that the studies quoted above looked at market integration across large wholesale markets that are well-connected by roads and communication flows. Differences in prices might emerge in more remote and isolated areas even for more commercial crops like maize and rice. We therefore considered studying the impact of the intervention on local market prices, particularly when the food purchased consists of food items that are not highly commercialised such as cassava and yam.

Impact on prices could, in principle, be observed through the household-level questionnaires. The farm gate price could be observed at the household level by including in the questionnaire questions related to prices paid and time of sales. This, however, would complicate the income section of the farmer questionnaire. Consumer prices are more difficult to observe in a standard household survey because the recall time is 7 or 30 days and there is only one survey per year. As part of the programme monitoring activities, price data will be collected, on a monthly basis, for main staple crops in the local market next to each of the selected schools for a sub-sample of farmer households. Collection of prices does not even require visits to markets if stable contacts can be established with collectors in each of the markets and prices could be communicated by phone.

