Haemoglobin levels (g/dL)	714	11.3 [1.34]	422	11.3 [1.35]	169	11.3 [1.36]	32	11.4 [1.47]	91	11.3 [1.21]	0.9088	0.8764	0.8469
Total maize production volumes (kg)	2626	787 [1751]	1163	864 [2034]	722	807 [1596]	375	590 [1248]	366	702 [1478]	0.0439	0.0376	0.2646
Total rice production volumes (kg)	2626	141 [652]	1163	149 [700]	722	148 [645]	375	137 [678]	366	111 [449]	0.6003	0.4551	0.5297
Total maize sale volumes (kg)	2626	393 [1196]	1163	432 [1261]	722	446 [1337]	375	270 [880]	366	292 [907]	0.1381	0.0057	0.7435
Total rice sale volumes (kg)	2626	84 [484]	1163	94 [583]	722	87 [413]	375	70 [397]	366	61 [327]	0.3509	0.2895	0.7286
Other variables													
Age (for 15 years and younger)	8407	7.5 [4.2]	3153	5.8 [9.0]	1918	6.2 [9.5]	942	6.2 [9.3]	917	6.1 [9.9]	0.057	0.847	0.8071
Is a girl? (for 15 years and younger)	8407	0.48 [0.5]	3799	0.48 [0.50]	2318	0.49 [0.50]	1167	0.47 [0.50]	1123	0.51 [0.5]	0.4933	0.9377	0.0989
Birth order (for all children)	8533	2.9 [2.0]	3791	2.9 [2.1]	2397	3.0 [2.0]	1189	3.0 [2.0]	1156	2.9 [1.9]	0.8275	0.021	0.2204
Is enrolled in school? (for 5–15 years)	6178	0.92 [0.27]	2755	0.91 [0.29]	1737	0.92 [0.26]	852	0.94 [0.01]	834	0.91 [0.29]	0.0375	0.9395	0.0065
Receives free school meals?	6280	0.19 [0.39]	2809	0.17 [0.38]	1768	0.23 [0.42]	860	0.13 [0.34]	843	0.24 [0.43]	0.0001	0.0055	<0.001
Distance to nearest school	6343	0.47 [3.24]	2765	0.45 [3.14]	1808	0.58 [4.34]	891	0.21 [0.85]	879	0.59 [2.29]	0.597	0.0992	<0.001
Time to school	6333	21.4 [45.6]	2778	19.6 [31.3]	1796	18.8 [32.5]	888	17.6 [22.7]	871	35.9 [95.1]	0.007	<0.001	<0.001
Total education expenditure	5635	23923 [35642]	2410	19250 [30878]	1640	27089 [37899]	789	25732 [37096]	796	29752 [40791]	<0.001	0.6249	0.0403
Mother’s education level (5–15 years)	5096	5.9 [9.4]	2290	5.7 [9.1]	1437	6.1 [9.6]	690	6.1 [9.4]	679	6.0 [9.8]	0.1946	0.8518	0.7608
Education level of head of household	2626	1.4 [2.6]	1163	1.4 [2.7]	1463	1.3 [2.5]	375	1.6 [2.7]	366	1.3 [2.2]	0.9393	0.2147	0.1344
Household size	2626	5.7 [2.4]	1163	5.7 [2.4]	722	5.8 [2.4]	375	5.7 [2.3]	366	5.6 [2.3]	0.8747	0.1774	0.5572
Per-capita expenditure quintile	2625	3.1 [1.4]	1162	3.2 [1.4]	722	2.9 [1.4]	375	3.3 [1.4]	366	3.1 [1.4]	0.1763	0.0008	0.2199
Household expenditure on food	2626	3473 [2187]	1163	3483 [2213]	722	3370 [2254]	375	3502 [1846]	366	3608 [2289]	0.815	0.1041	0.4874
Household expenditure on health	2626	93.5 [112]	1163	97.7 [116]	722	88.7 [107]	375	93.3 [108]	366	90.0 [112]	0.0894	0.595	0.6768

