Household expenditure on education	2626	214 [333]	1163	204 [328]	722	195 [311]	375	233 [340]	366	260 [374]	0.1926	0.0034	0.3013
Household expenditure on transport	2626	317 [415]	1163	315 [407]	722	297 [393]	375	352 [447]	366	326 [447]	0.8157	0.0607	0.4316
% share of HH expenditure spent on food	2626	59.8 [15.8]	1163	59.6 [16.4]	722	60.3 [15.4]	375	58.0 [14.0]	366	61.1 [16.0]	0.5613	0.3073	0.0049

Estimates are expressed as mean and standard deviation

*BMI* body mass index, *HH* household. * T-test statistics for comparisons across treatment arms

In the education domain, 92 % of children aged 5–15 years were enrolled in school, and mean enrolment rates were marginally lower in the control population (0.91, SD 0.29) compared to the school feeding group (0.93, SD 0.26). Significant differences were also found for age of first enrolment, the number of times that a year was repeated, and across all the four test scores.

In the nutrition domain for children aged 5–15 years, the mean z-scores for the anthropometrics measures of height for age and BMI for age were −0.925 (SD 1.35) and −0.592 (SD 0.924) respectively, with significant differences across the GSFP versus HGSF comparison groups. Iron status, as measured through haemoglobin levels, for the sub-sample of children (*n* = 714) who were assessed, was on average 11.3 g/dL (SD 1.34), just below the 11.5 g/dL cut-off for non-anaemia in the 5–11 years age group.

In terms of household socio-economic characteristics, there were neither significant differences among the treatment groups for the mean education levels of mothers and household heads, nor for household size. There was, however, a significant difference in terms of per-capita household expenditure quintiles between households in the GSFP and HGSF groups, but no other substantive differences with regards to household expenditure were observed.

In the agriculture domain, across the survey population the mean production of maize over the previous 12 months was 787 kg (SD 1751), with average household sales of maize during the same period of 393 kg (SD 1196). Mean household production of rice was 141 kg (SD 625), with average annual sale volumes of 84 kg (SD 484). Significant differences were found across treatment arms in terms of maize production and sales.

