#### Farm income

We used data from GLSS4 of 1998/1999 to estimate average farm income of rural households (1200 cedis) and relative SD (1400 cedis). We found an extremely high ICC. Income is the most difficult outcome to estimate with sufficient precision. The chart below plots the standardised minimum detectable difference against the number of clusters assuming 20 farmers interviewed in each community. Since the SD is roughly similar to the mean the vertical axis can be interpreted as a percentage difference (Fig. 8).

The table below summarises the standardised differences and the corresponding percentage changes in income that can be estimated with different study designs (Table 11).

**Table 11 Tab11:** Farm income: standardised detectable differences and equivalent levels for different designs

	Farm incomes (in SDs)	Percentage difference
30 clusters	0.6	0.69
60 clusters	0.4	0.46
120 clusters	0.3	0.35

*SD* standard deviation

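### The primary agricultural outcome is farm income among farmers in the abstract and Appendix 1, but household income, production and sales with no stated population in Table 1

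*Protocol article*

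**What the plan says.** - **Abstract:** "Primary outcomes include child health and nutritional status, school participation and learning, and smallholder farmer income".
- **Table 1**, headed "Primary indicators for the evaluation": the agriculture row reads "Household income, production, sales". Age ranges are given for education, cognition and nutrition; the agriculture row has no population.
- **Text below Table 1:** it returns to farmer income and counts "market access (marketed surplus, prices and markets" among the intermediate outcomes, although the table lists sales as a primary impact indicator.
- **Table 3:** the metric for income is farm profits.
- **Appendix 1, Farm income:** survey data were used to "estimate average farm income of rural households", and detectable differences assume 20 farmers interviewed per community.
- **Table 4:** farm income (revenues, input expenditure, depreciation) is a separate module from wage work, own business and other income such as transfers and remittances.
- **Sample sizes:** 10 of 25 households in intervention communities and 5 of 20 in control communities are sampled as farmers.

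**The concern.** The article presents the effect on agriculture as the trial's new question, yet it leaves open which variable answers it and in whom. The candidates are not interchangeable. Household income adds sources the programme may not touch. Production and sales are gross quantities with no deduction for inputs. A farmer analysis and an all-household analysis estimate different averages.

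Two things are at stake. The first is interpretation: with several measures labelled primary and no population fixed, the choice could be made after the endline data are seen. The second is precision and bias. The article expects only a small number of farmers to be affected, so averaging over mostly non-farmer households shrinks the effect. Because the farmer share differs by design between intervention and control communities, an unweighted comparison also mixes a composition difference into the contrast.

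**Working it through.** **1. The plan's own figure.** Appendix 1 gives mean farm income 1200 cedis and SD 1400 cedis. Table 11 gives 0.6, 0.4 and 0.3 SD for 30, 60 and 120 clusters. Multiplying by 1400/1200 gives 0.70, 0.467 and 0.35, against the printed 0.69, 0.46 and 0.35. The conversion reproduces to rounding.

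The SD figures cannot be reproduced directly because no ICC is given. Assume two-sided 5%, 80% power and equal allocation, and solve

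MDD = 2.80 × √[(4/J) × (ρ + (1 − ρ)/20)]

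for ρ:
- J = 30, MDD 0.6: ρ = 0.31
- J = 60, MDD 0.4: ρ = 0.27
- J = 120, MDD 0.3: ρ = 0.31

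An ICC of 0.27–0.31 is used below.

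**2. Farmer mix.** Intervention: 10/25 = 40%. Control: 5/20 = 25%. Over 58 communities each, farmers number 58 × 10 + 58 × 5 = 870 of 58 × 25 + 58 × 20 = 2610 households, one third.

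**3. Dilution (illustration).** Assume a 0.35 SD effect in farmers, none in other households, the same SD and ICC in both populations, and no credit for district pairing. SE² = Σ over arms of (ρ + (1 − ρ)/m)/58, and power = Φ(effect/SE − 1.96).

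| Analysis | m per community | SE (ρ = 0.27, 0.31) | Effect | Power |
|---|---|---|---|---|
| Farmer stratum | 10 v 5 | 0.114, 0.119 | 0.35 SD | 86%, 83% |
| All households | 25 v 20 | 0.102, 0.108 | 0.40 × 0.35 = 0.14 SD | 28%, 25% |

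The multiplier is 40% because only the intervention communities' farmers can gain.

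**4. Unequal mix (illustration).** With no treatment effect, an unweighted endline difference in farm income over all households equals (0.40 − 0.25) × the gap in mean farm income between farmers and others. With 1200 cedis for farmers and, as an extreme, zero for others, that is 0.15 × 1200 = 180 cedis, or 180/1400 = 0.13 SD. This is about the size of the diluted true effect in step 3. It arises only against control: GSFP and HGSF communities both have 10 farmers in 25.

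**5. Household income (illustration).** If farm income is 30%, 50% or 80% of household income (share not given; range assumed) and other income is unchanged, a 35% farm-income gain becomes 10.5%, 17.5% or 28%.

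**6. Reach of Table 11.** SD/mean is 1400/1200 = 1.17 for farm income. In the all-household baseline data it is 1751/787 = 2.2 for maize production, 1196/393 = 3.0 for maize sales, 652/141 = 4.6 for rice production and 484/84 = 5.8 for rice sales. Table 11's percentages therefore do not carry over to volumes, and the article gives no mean, SD or ICC for household income. Even for farm income, Table 11 assumes 20 farmers per community. With the sampled 10 and 5, the detectable difference for school feeding against control is 2.80 × 0.114 to 2.80 × 0.119 = 0.32–0.33 SD (37–39%).

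**The case against.** The labels are closer than they first appear. The Table 4 farm module records revenues, inputs and depreciation, so farmer income, farm income and farm profits can all be one net measure. What remains is Table 1 against the rest. That is accepted, and it narrows the point.

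Household income also has a stated purpose. The programme theory aims to support both recipient and farmer households, and the hypotheses allow that others in the community may gain. It should therefore be kept, but as its own labelled outcome.

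The planned difference-in-difference and ANCOVA analyses use baseline values and would remove much of the level difference in step 4. They do not undo dilution. Nor do they remove a change over time that is common to farmers, which would leave 0.15 times that change in an unweighted difference-in-difference.

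Derivations and populations are often left to an analysis plan. Here, however, the article contradicts itself on which variable is primary, so this is not merely omitted detail.

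Three stronger readings are tempting and should not be drawn:
- **That Table 6 redefines the primary outcome as crop weight over everyone.** Rows such as "Total maize production volumes (kg" and the statement that "across the survey population the mean production of maize over the previous 12 months was 787 kg" belong to a baseline table and fit the production and sales part of Table 1. Nothing calls them primary.
- **That the article identifies tubers as the crops where farmers would gain.** The Markets section mentions "food items that are not highly commercialised such as cassava and yam" in connection with local prices, not farmer income.
- **That the measures would give different answers at endline.** They could. For GSFP against HGSF at baseline, maize sales give p = 0.0057 and rice sales p = 0.2895, but these tests ignore clustering and say nothing about endline effects.

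**Conclusion.** The inconsistency is real and nothing in the article resolves it. Farm income among farmers is the outcome of the abstract and the power calculation; Table 1 substitutes household income, production and sales, with no population, while the text beneath it calls marketed surplus intermediate. The 40% and 25% farmer shares are fixed by the sampling design, so the dilution and the unequal mix in an unweighted all-household comparison with control follow directly.

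Their size is less certain. The fall from about 83–86% to 25–28% power, and the 10.5–28% range for household income, rest on an ICC back-solved from rounded figures, equal SDs and ICCs in both populations, no effect outside the farmer stratum, and assumed income shares. They show that the choice matters and do not predict the trial's power. This should be settled before the endline analysis; it does not undermine the design.

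**What to change.** In Table 1, name the primary agricultural outcome as net farm income (revenues less input expenditure and depreciation, from the Table 4 module) in households sampled in the farmer stratum. This matches the abstract, Table 3 and the outcome and unit of Appendix 1. Then:

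- Keep total household income as a separately labelled secondary outcome for the recipient-household aim, and weight or adjust any all-household analysis for farmer stratum.
- Make production and sales volumes secondary or intermediate, consistent with the text below Table 1.
- State that Table 11 applies to farm income among farmers only, and restate it for 10 and 5 farmers per community.

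The cost is wording and one derived variable. The downside is that a monetary measure is likely to be noisier than crop volumes, and the appendix itself says income is the hardest outcome to estimate precisely. That is a reason to report volumes alongside it, not to leave the primary outcome open.
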